#### Methods of Data Analysis

**1.a. Sample Size – Quantitative**

Sample size calculations for Aim 1 assume that the background annual incidence rate for HSV-2 is 16% (corresponding to a prevalence rate following two years of follow-up of approximately 22%), and that participants will be followed for three years. Further, we conservatively assume that 20% of participants will be lost to follow-up (our average loss to follow-up over all completed studies is 12% [C.1]). Although individuals will form the unit of randomization, the fact that they will be associated via membership in life skills cohorts may induce correlation between individual outcomes within groups (assumed to include an average number of 25 girls) –We account for this using methods described in Hayes and Bennett [77], which take into account both the number of individuals randomized into each arm and the between-group variation in incidence rates induced by within-group correlation in infection outcomes. Incidence rates will be compared between arms using a two-sample t statistic adjusted to account for this source of variation. The corresponding coefficient of variation is assumed to be 0.2, a conservative estimate similar to values used in other studies [77, 78]. With these assumptions, our proposed sample size **of 300 (150** individuals randomized to each arm) will provide 80% power to detect a relative reduction in HSV-2 incidence as small as .53 at the 5% significance level. This corresponds to a 47% reduction in HSV-2 incidence (from 12% to 6.3%). Because unintended pregnancy is expected to have similar, if not higher incidence rates, the above calculations apply to this outcome as well.

Similar calculations for the HIV infection outcome (at 8% prevalence) indicate that we should have 80% power to detect a relative risk comparing incidence in the intervention group to the control group as small as .29 at the 5% significance level. This corresponds to a 70% absolute reduction in HIV incidence, assuming a background annual HIV incidence rate in the target communities of approximately 4%. This is an effect we do not expect to be able to detect given our sample size. We will, however, be able to report trends. The high prevalence rates cited in section B.1. were among young females in an antenatal clinic who were obviously sexually active and practicing unprotected sex. Among adolescents in Zimbabwe, HSV-2 rates tend to be three to five time higher than HIV rates [10].

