**C. Subject Selection**

i. Main Study

**1. Who and Why**: The target population for the study is out-of-school adolescent female orphans living in urban -Zimbabwe. Females aged 16 to 19 years will be recruited. We restricted the intervention to females because prevalence data clearly show that girls are at higher risk for HIV infection. We hypothesize that an economic livelihood intervention will have greater effect on our biological and behavioral outcomes in females, as it will create alternatives to transactional sex, which is overwhelmingly practiced by females for accessing resources and gaining status. Sixteen is the legal age of consent in Zimbabwe, thus, we are able to collect and test biological specimens and provide results without obtaining parental or /guardian consent. We have chosen our upper age range as 19 because this is consistent with literature on the definition of adolescents [69]. We have restricted our sample to those girls not currently in school, and who have not already graduated from secondary school. The vulnerability of out of school girls (reflected through current HIV trends) also indicates a lack of access to: knowledge of health risks, skills in communication and negotiation, and to condoms and youth friendly services, which provide needed services at a convenient time and place, in a manner that satisfies adolescents’ concern over confidentiality [70, 71].

**2. Numbers**: One hundred fifty individuals will be randomly assigned to the treatment arm and 150 to the control arm, for a total of 300 participants.

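### The sample-size paragraph equates 16% annual HSV-2 incidence with about 22% at two years; 16% gives 27–29%, and the 22% and the stated effect fit about 12% a year instead

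*Protocol*

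**What the plan says.** All the figures are in the Protocol, Methods of Data Analysis, 1.a. Sample Size – Quantitative, in the paragraph on Aim 1.

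- Base rate: the calculations "assume that the background annual incidence rate for HSV-2 is 16" per cent.
- Its stated equivalent, in the same sentence: "corresponding to a prevalence rate following two years of follow-up of approximately 22" per cent.
- Follow-up used for sizing: "and that participants will be followed for three years".
- Detectable effect, for 80% power with 150 girls per arm: the trial could "detect a relative reduction in HSV-2 incidence as small as .53 at the 5% significance level". The next sentence shows that .53 is the ratio of the two incidences, not the reduction.
- The effect in percentages: "This corresponds to a 47% reduction in HSV-2 incidence (from 12% to 6.3" per cent), with no time unit.

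The paragraph also assumes 20% loss to follow-up, life-skills groups of 25 on average and a between-group coefficient of variation of 0.2. It applies the whole calculation to unintended pregnancy, the other primary outcome. Nothing in the protocol links 16% to 12%.

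**The concern.** The sentence offers 16% a year and 22% at two years as one assumption expressed in two ways. Under section C, Inclusion/Exclusion Criteria, girls in the main study are HSV-2 negative at entry, so prevalence at two years among those followed is two-year cumulative incidence and can be calculated directly from the annual figure. It does not come to 22%. The effect is then stated from 12%, not 16%.

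The base rate sets the expected number of primary events and, with the other inputs, the smallest detectable effect. Because the paragraph extends the calculation to unintended pregnancy, both Aim 1 outcomes depend on it. Anyone who later interprets a null result, or checks observed control incidence against the plan, will probably take the opening 16% as the planning value, while the effect printed a few lines later starts from 12%.

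**Working it through.** **1. Inputs.** From section 1.a: annual incidence 16%; two-year figure 22%; effect from 12% to 6.3%, ratio 0.53; loss 20%; groups of 25; coefficient of variation k = 0.2; 5% significance; 80% power. From section C, Numbers: 150 per arm. Hence 150 / 25 = 6 groups per arm, 25 × 0.8 = 20 girls analysed per group, and 150 × 0.8 = 120 per arm. Assumption: the 5% is two-sided, which the text does not say.

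**2. Annual figure to two-year figure.** If r is a rate, the two-year risk is 1 − exp(−2r). If r is an annual risk, it is 1 − (1 − r)².

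| Annual figure | As a rate | As an annual risk |
|---|---|---|
| 16% | 1 − exp(−0.32) = 27.4% | 1 − 0.84² = 29.4% |
| 12% | 1 − exp(−0.24) = 21.3% | 1 − 0.88² = 22.6% |

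Working back from 22%: −ln(0.78) / 2 = 12.4% a year as a rate, or 1 − √0.78 = 11.7% as an annual risk. Simple addition gives 2 × 16% = 32%, which is further from 22%.

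**3. The stated effect.** 6.3 / 12 = 0.525, which agrees with 0.53 and a 47% reduction within rounding. The effect sentence is therefore consistent with a 12% base, and 12% read as annual is consistent with 22% at two years.

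**4. A comparison within the section.** The HIV paragraph gives 4% a year and a prevalence of 8%. Over two years, 4% gives 1 − exp(−0.08) = 7.7% or 1 − 0.96² = 7.8%. That pair agrees on the ordinary conversion; the HSV-2 pair does not.

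**5. Expected control infections**, 120 × [1 − exp(−r × years)]:

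| | 16% a year | 12% a year |
|---|---|---|
| Two years | 32.9 | 25.6 |
| Three years | 45.7 | 36.3 |

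At two years the higher rate gives 32.9 / 25.6 = 1.28 times as many events.

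**6. Detectable ratio.** The cited Hayes–Bennett formula for rates is c = 1 + (1.960 + 0.842)² × [(r0 + r1)/y + k²(r0² + r1²)] / (r0 − r1)², where c is the number of groups per arm and y the person-years per group. It is solved for r1/r0 with c = 6, k = 0.2 and y = 20 × years (40 or 60). Both lengths are shown because the sizing uses three years while General Study Design describes one year of intervention and one year after it.

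| | 16% a year | 12% a year | Difference |
|---|---|---|---|
| Two years | 0.363 | 0.298 | 0.065 |
| Three years | 0.442 | 0.388 | 0.054 |

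None of these equals the printed 0.53, so the plan's own figure is not reproduced from either rate with the stated inputs. The last column is the part that the choice of base rate accounts for.

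**The case against.** The best defence is that the paragraph is more coherent than it looks. The 12% and the 22% agree, the effect is expressed from 12%, and a careful reader can see which base the effect sentence uses. That stands. A reader might infer three rival rates and no usable base rate at all, but the text does not support this: there are two rates, and one of them fits everything except the opening figure.

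It is also fair that 12% a year is a reading, because the text prints no time unit. If 12% is not annual, the link from 12% to 22% falls away, but the mismatch between 16% and 22% remains.

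The 16% can be brought to 22% by other routes. Counting the 20% lost as uninfected gives 0.8 × 27.4% = 21.9%. A mean exposure of −ln(0.78) / 0.16 = 1.55 years also gives 22%. The protocol states neither. The first is not a prevalence among those followed, it uses a loss that the text introduces as a separate assumption, and it does not explain the 12%.

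Finally, the practical reach is limited. General Study Design reports main-study enrolment complete at 315, and the primary analysis in section 2, Data Analysis (Poisson regression with GEE) does not use the planning rate. Both points stand, and they keep this a correction of the record.

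**Conclusion.** Wrong as written. An annual HSV-2 incidence of 16% does not correspond to about 22% at two years; it gives 27.4% or 29.4%. The paragraph contains two incompatible base rates, 16% and about 12%. The 16% is the outlier and the more favourable: about 28% more control infections over two years (33 against 26), and a detectable ratio nearer to 1 by about 0.05–0.07 at fixed follow-up.

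The mismatch between 16% and 22% needs no assumption beyond girls being uninfected at entry. Pairing 22% with 12% assumes that 12% is annual. The detectable ratios assume a two-sided 5% test, six groups per arm and 20 analysed girls per group.

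A reader might go further and blame the base rate for the failure to reproduce 0.53. The figures do not support that. Changing the rate moves the ratio by 0.05–0.07, while the gap to 0.53 is 0.53 − 0.442 = 0.09 at its smallest and 0.53 − 0.298 = 0.23 at its largest. Most of the gap therefore has other causes at either length of follow-up. The failure to reproduce 0.53 and the two-year against three-year follow-up are separate questions.

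**What to change.** 1. State one annual HSV-2 incidence, say whether it is a rate or an annual risk, and give its correct two-year equivalent: 12% with about 21–23%, or 16% with 27–29%.
2. Recompute the detectable ratio from that rate with the stated inputs, for HSV-2 and for unintended pregnancy, and state the length of follow-up used.
3. Derive the before-and-after incidences from the recomputed ratio, with a time unit. With the inputs above, 12% would fall to 0.388 × 12% = 4.7% over three years or 0.298 × 12% = 3.6% over two. For 16% the figures are 0.442 × 16% = 7.1% and 0.363 × 16% = 5.8%.
4. Do not keep 0.53 and apply it to the chosen rate. For example, 0.53 × 16% = 8.5% would print an effect that the stated inputs do not deliver.

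The cost is a few words and one recalculation in the sample-size section. If 12% is chosen, the stated planning rate becomes less favourable. Enrolment, conduct and the primary analysis are unchanged.

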**4. Methods**

**A. General Study Design**

We propose a randomized controlled trial of an intervention combining a vocational training package -- including a conditional stipend and completion bonus -- with life-skills education and social support, compared to life-skills education alone. The study will begin with six months of start-up activities, and enrollment will take place within a six-month period at the beginning of the study. The economic livelihood intervention and life-skills programs will be administered for one year and participants will be followed for one year post-intervention. Data collection and service provision to participants will be provided through a health clinic and occasional visits using a mobile clinic. The frequency of intervention visits (i.e. visits related to the intervention program such as life-skills training, SHAZ reunions, and vocational training) is described below. Visits for data collection, including biological and behavioral outcome data, will be collected at baseline, and every six months thereafter for a total of five visits over the three year period. We will follow participants for one year after the intervention to ensure sufficient power to examine our primary outcome (Aim 1) as well as to establish the temporal association between the intermediary effects of increased economic opportunity and improved sexual negotiation skills in enhancing participants’ control over sexual interactions (Aim 3). Finally one year of follow-up will allow us to assess the intervention’s sustained effects on high-risk behavior (Aim 2). (Please see appendices: Intervention Design and Study Design Flow Chart)

**Prevention for Positives component:** The SHAZ main study has completed its enrollment for the ongoing intervention study, with a total of n=315. In order to assess the feasibility of implementing this intervention with HIV and HSV-2 positive clients, we will enroll an additional cohort of n=50 according to the same criteria as was used in the main study, except that those who are HIV and/or HSV-2 positive also will be eligible to enroll.

In order to meet this objective, we will contact and invite all participants who screened out of the study because of positive results (n=40) and invite these to re-screen for the study. We will then continue to recruit additional participants until we meet the desired sample size n=50.

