We will randomize participants into intervention and control arms, as per the main study, and deliver the intervention, study visits and data collection activities according to existing SHAZ protocols**. The exception is that the Prevention for Positives cohort will have only two follow up visits instead of three.** The participants of this feasibility study will then participate in the intervention just as is described in detail in the original main study protocol.

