**E. Consent Process and Documentation**

All potential study participants will have the opportunity to meet with study staff one-on-one to learn about the study and ask questions for clarification. The participants will be told that they are being asked to participate in a confidential study about improving economic opportunities and reproductive health among adolescent female orphans. They will be told that participation involves periodic interviews and biological sample collection for HIV, HSV-2 and pregnancy testing, whether or not the participant is sexually active. Randomization will also be explained and participants will be told that if they participate, and if they are selected for the control group, they will receive the economic component of the intervention after the study is complete, assuming we observe an efficacious result. They will be told that some of the questions examine high-risk sexual behaviors, as well as other sensitive issues. They will be told that trained nurse/counselors will collect biological specimens and administer data collection surveys every six months for a period of three years.Participants will be told that they have the right to refuse or withdraw from the study at any time. The research objectives, the tests performed, and the names and telephone numbers of the interviewer and local principal investigator/project director will be told verbally to all participants, and summarized in an “information sheet,” with which they will be provided. If the individual is eligible and agrees to participate, study staff will explain the terms of the study’s consent form. If the prospective participant consents, she will be asked to sign the consent form. The consent form will be available in Shona and English. It may be intimidating for young people to sign a consent form, and they may feel that it will impinge upon confidentiality. Thus, participants who feel uncomfortable signing the consent form will be asked to put a mark (but no signature) at the bottom of the document to denote their consent.

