Once making her selection, the participant will be placed in one of the three training courses that will take place over a 6-month period with the objective to acquire vocational skills and practice life skills. Based on monthly assessments of attendance, training fees will be paid directly to institutions and participants will receive a stipend for transport and basic food requirements. Fees and stipends will be withdrawn if the participant does not attend at least 80% of the sessions. If participant falls ill or is otherwise unable to attend for legitimate reasons, participants will be allowed to make up sessions. The participant is also required to meet with her guidance counselor at least once. At the end of the training session, if the participant attended at least 80% of the sessions, passed the final exam and made guidance counselor contact she will be eligible for a bonus (equivalent to US$100), contingent upon working with her guidance counselor to develop a plan to use this bonus towards ongoing education, accessing credit or starting up a business using her acquired skills or to secure employment. The participant will have two chances to pass her final examination. At this stage, the guidance counselor will assist the participant in linking to jobs, accessing further training and micro-credit as appropriate. Throughout the course of the study, staff will have ongoing contact with the participant during SHAZ! reunions with her initial life skills class and study visits at alternating 6 month intervals.

ii. Control Group

The control group will have a comparable experience for all aspects of the intervention, except for the vocational training and accompanying monthly fees, stipend and completion bonus, and the personalized guidance counseling. After the first year of the study, the intervention will no longer be delivered. We will follow-up participants from both arms for one additional year, conducting follow-up ACASI interviews and the same biological tests every six months.

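### The Aim 1 power calculation credits each participant with three years of follow-up where the design gives two; the stated 80% power is not met at two years, and the stated inputs do not reproduce it at three

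*Protocol*

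**What the plan says.** Section 1.a (Sample Size – Quantitative) lists among its inputs that "participants will be followed for three years". The other inputs are 150 per arm, 20% loss to follow-up, life-skills groups averaging 25, a between-group coefficient of variation of 0.2 and the 5% level. From these it claims 80% power for a relative HSV-2 incidence of 0.53. It carries the calculation over to unintended pregnancy and makes a similar one for HIV.

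The design is described differently. Section 4.A (General Study Design): "The economic livelihood intervention and life-skills programs will be administered for one year and participants will be followed for one year post-intervention". Section F.1 repeats that there is one year of follow-up after the first-year intervention, and its Control Group paragraph says "We will follow-up participants from both arms for one additional year". Section 4.A sets data collection "at baseline, and every six months thereafter for a total of five visits over the three year period".

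Two further statements bear on duration. Section E (Consent Process) says that participants will be told that staff will "administer data collection surveys every six months for a period of three years". The Prevention for Positives text says that the added cohort "will have only two follow up visits instead of three".

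**The concern.** Section 2 (Data Analysis) compares HSV-2 incidence by Poisson regression, to allow for length of follow-up. Person-time therefore drives the expected number of events and the precision of the comparison. Section 4.A itself justifies the post-intervention year as securing power for the primary outcome. If the calculation counts a third year that the design does not contain, the power stated for both primary outcomes is too high. The trial could then be reported as having had 80% power for a 47% reduction when it had much less. The consent section also describes a longer commitment than the schedule requires.

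**Working it through.** **1. Duration.** One year of intervention plus one year after it is 24 months. Five visits at six-month spacing fall at months 0, 6, 12, 18 and 24. Three years at the same spacing would need seven visits (0 to 36). Three places (4.A, F.1 and its Control Group paragraph) and the visit count agree on two years. The three-year figure appears in 1.a, in Section E and as the label on the five-visit schedule in 4.A.

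**2. Person-time per arm.** 150 × 0.80 = 120 retained.
- Three years: 120 × 3 = 360 person-years. Two years: 120 × 2 = 240. Ratio 1.50.
- Counting time only to infection, mean time at risk is (1 − e^(−λT))/λ. At λ = 0.16 this is 2.383 years (T = 3) against 1.712 (T = 2), ratio 1.39. At λ = 0.0636 it is 2.731 against 1.878, ratio 1.45. Hence 39-45%.

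**3. Control rate.** Section 1.a gives 16% per year but states the effect as 12% to 6.3%. Its two-year figure of about 22% fits 12% (1 − 0.88² = 22.6%), not 16% (1 − 0.84² = 29.4%). Both rates are carried below.

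**4. Power formula.** The Hayes-Bennett rate formula, solved for power:

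z² = (c − 1)(λ0 − λ1)² / [(λ0 + λ1)/y + k²(λ0² + λ1²)], power = Φ(z − 1.96)

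Here c = 150/25 = 6 groups per arm, y = 20 × T person-years per group (25 less 20% loss), k = 0.2 and λ1 = 0.53 λ0. The test is taken as two-sided, which the protocol does not state. The version without the +1 cluster term replaces c − 1 by c.

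**5. The plan's own figure, T = 3 (y = 60).**
- λ0 = 0.16, λ1 = 0.0848: (λ0 − λ1)² = 0.005655; variance term 0.00408 + 0.00131 = 0.00539. With +1, z = 2.29, power 63%. Without, z = 2.51, power 71%.
- λ0 = 0.12, λ1 = 0.0636: 0.003181; 0.00306 + 0.00074 = 0.00380. With +1, z = 2.05, power 53%. Without, z = 2.24, power 61%.

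The stated 80% is not reproduced. A value near it appears at three years only if a stated assumption is dropped, for example 12% per year with no loss and no clustering (79.7%), or 16% per year with loss but no clustering (82%).

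**6. The design as written, T = 2 (y = 40).**
- λ0 = 0.16: variance term 0.00612 + 0.00131 = 0.00743. z = 1.95 or 2.14, power 50% or 57%.
- λ0 = 0.12: 0.00459 + 0.00074 = 0.00533. z = 1.73 or 1.89, power 41% or 47%.

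| Control rate | Power, 3 years | Power, 2 years | Rate ratio with 80% power, 2 years |
|---|---|---|---|
| 16%/year | 63-71% | 50-57% | 0.36-0.41 |
| 12%/year | 53-61% | 41-47% | 0.30-0.35 |

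Ranges are with and without the +1 term. Moving from three years to two costs about 13-14 points in each case.

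**7. Sensitivity.** With no loss at all and no +1 term, two-year power is 65% (16%) or 55% (12%). The highest two-year value found with k = 0.2 and a two-sided test is 67%. It takes 16% per year, no loss, the 315 actually enrolled, no +1 term and the log-rate scale.

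**The case against.** The strongest reply concerns cause. A reader might infer that the missing third year is why 80% power fails, especially from the unclustered figures at 16% per year (82% at three years, 65% at two). The document does not support that. Section 1.a says that the grouping adjustment was applied, and with it the stated inputs fall short of 80% at three years as well. Duration adds to a shortfall that is already there. This objection stands and limits the claim.

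A reader might also take the three years to be the project calendar: six months of start-up, six of enrolment and 24 of follow-up. The sum fits, but the protocol never says so, and Sections 4.A and E attach three years to data collection. It remains an inference. What can be shown is a contradiction in which two years is the better-supported reading.

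The Prevention for Positives text might look like the same error again. It is not: it implies three main-study follow-up visits, fewer than the four in 4.A, so it errs in the opposite direction.

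On size, the calculation gives lost participants no time at all, whereas a Poisson analysis would use their time up to loss. That is fair, but even with no loss two-year power stays well below 80%. For HIV little turns on the correction, because the protocol already says that it is not powered for that outcome. Enrolment is complete at 315, and neither the analysis method nor the sample size changes. How readers would interpret a null result cannot be shown from the document.

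**Conclusion.** The concern holds in a limited form. Section 1.a uses three years per participant and the design provides two, which overstates nominal person-time by 50% (39-45% to infection). At two years, power for a rate ratio of 0.53 is about 50-57% at 16% per year or 41-47% at 12%. The 80% statement is therefore wrong as written. The shorter duration accounts for about 13-14 points; the rest of the gap is present at three years on the plan's own inputs.

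These figures assume a two-sided test, six equal groups per arm, 20 retained per group and no person-time from those lost. No single figure can be given until the control rate is settled.

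**What to change.** 1. Settle the control rate in Section 1.a: 16% per year, or the 12% that the stated effect and the 22% two-year figure imply.
2. Recompute Section 1.a on 24 months per participant with the stated loss and clustering, and state the sidedness and the form of the cluster formula.
3. Replace the sentence claiming 80% power for 0.53 with the resulting power, or with the rate ratio detectable at 80% power (about 0.36-0.41 at 16%, 0.30-0.35 at 12%). Apply the same correction to the pregnancy and HIV statements.
4. Reconcile the three-year wording in Sections 4.A, 1.a and E with the two-year design, including what participants are told at consent.
5. Separately, reconcile the three main-study follow-up visits implied in the Prevention for Positives text with the four in Section 4.A.

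The cost is a recalculation, amended protocol and consent wording, and a less favourable power statement. No added enrolment or visits are needed.

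### The stated 80% power for an HSV-2 rate ratio of 0.53 with 150 girls per arm does not follow from the plan's own inputs, which give about 53% at 12% a year or 63% at 16%

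*Protocol*

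**What the plan says.** Protocol, section 1.a (Sample Size – Quantitative), opens with the control rate. The calculations "assume that the background annual incidence rate for HSV-2 is 16" per cent, "corresponding to a prevalence rate following two years of follow-up of approximately 22" per cent. The other inputs are three years of follow-up, 20% loss, life-skills groups averaging 25 girls, the Hayes and Bennett method with a two-sample t statistic, and a 5% level. On clustering it says: "The corresponding coefficient of variation is assumed to be 0.2, a conservative estimate".

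The conclusion concerns 300 girls, 150 per arm: "individuals randomized to each arm) will provide 80% power to detect a relative reduction in HSV-2 incidence as small as .53 at the 5% significance". The next sentence reads: "This corresponds to a 47% reduction in HSV-2 incidence (from 12% to 6.3" per cent). So .53 is a rate ratio, although the text calls it a relative reduction, and the control rate is now 12%, not 16%. The same calculation is then extended to unintended pregnancy. For HIV, at 4% a year, the section gives a detectable relative risk of .29.

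Section C (Subject Selection, Numbers) confirms the size: "One hundred fifty individuals will be randomly assigned to the treatment arm and 150 to the control arm, for a total of 300 participants". Section A (General Study Design) describes one year of intervention and one year of follow-up after it, and reports 315 enrolled in the main study.

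**The concern.** The paragraph names its method and most of its inputs, so the 80% can be checked without an SAP. Six groups per arm is a small number for a method that counts groups, and the paragraph gives two control rates.

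This is the only power statement for the two primary outcomes, HSV-2 and unintended pregnancy. The protocol warns that HIV is underpowered but presents HSV-2 as adequately powered. If the 80% is wrong, a reader of a non-significant result could take it as evidence against a 47% reduction when the planning figures do not support that.

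**Working it through.** **Inputs (section 1.a).** 150 girls per arm in groups of 25 gives c = 150/25 = 6 groups per arm. Person-years per group: y = 25 × 0.8 × 3 = 60. Between-group coefficient of variation k = 0.2. Rate ratio 0.53. Control rate λ0 = 0.12 or 0.16. Assumed because the text does not say: a two-sided test, and the 20% loss removing its full person-time.

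**Formula** (Hayes and Bennett, rates, unmatched groups):

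c = 1 + (z_α/2 + z_β)² × R, where R = [(λ0 + λ1)/y + k²(λ0² + λ1²)] / (λ0 − λ1)².

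Solved for power: Φ(√((c − 1)/R) − 1.96).

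**Attempt to reproduce the 80%.**

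- 12%: λ1 = 0.53 × 0.12 = 0.0636. R = (0.1836/60 + 0.04 × 0.01844)/0.00318 = 1.194. Power = Φ(√(5/1.194) − 1.96) = Φ(0.086) = 53%. For 80% power, c = 1 + 7.85 × 1.194 = 10.4 groups per arm.
- 16%: λ1 = 0.0848. R = (0.2448/60 + 0.04 × 0.03279)/0.005655 = 0.953. Power = Φ(√(5/0.953) − 1.96) = Φ(0.33) = 63%. For 80% power, c = 8.5 groups per arm.

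A noncentral t with 10 degrees of freedom gives 52.6% and 61.9%. Using the 315 enrolled gives 56% and 65%. The 80% is not reproduced.

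**Detectable ratio at 80% power, six groups per arm.** This needs √(5/R) = 1.96 + 0.84, so R = 5/7.85 = 0.637. The solution is a ratio of 0.39 at 12% (a 61% reduction) and 0.44 at 16% (a 56% reduction).

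**Sensitivity to what the text leaves open** (three years, k = 0.2, ratio 0.53):

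| Reading | 12% | 16% |
|---|---|---|
| Two-sided, +1 term, full 20% loss | 53% | 63% |
| Two-sided, +1 term, half the lost time kept | 57% | 67% |
| Two-sided, +1 term, no loss | 61% | 70% |
| Two-sided, no +1 term, full loss | 61% | 71% |
| Two-sided, no +1 term, no loss | 69% | 78% |
| One-sided, +1 term, full loss | 66% | 74% |
| One-sided, no +1 term, full loss | 73% | 81% |
| One-sided, +1 term, no loss | 72% | 80% |

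**Two years of follow-up, as in the design section** (y = 25 × 0.8 × 2 = 40). At 12%, R = (0.1836/40 + 0.04 × 0.01844)/0.00318 = 1.675 and power is Φ(√(5/1.675) − 1.96) = 41%. At 16% it is 50%. The detectable ratios are about 0.30 and 0.36.

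**Background rate.** Two-year cumulative incidence at 16% a year is 1 − exp(−0.32) = 27.4%, or 1 − 0.84² = 29.4%. At 12% it is 1 − exp(−0.24) = 21.3%, or 1 − 0.88² = 22.6%. The printed 22% therefore fits 12%, as does the drop from 12% to 6.3%; neither fits 16%.

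**Cross-check on the printed effects.** With 10 groups (250 girls) per arm, three years and otherwise the same inputs, the detectable ratio is 0.52 for HSV-2 at 12% and 0.29 for HIV at 4%, close to the printed .53 and .29. With six groups the HIV figure would be about 0.11.

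**The case against.** Several points on the other side are fair.

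- *The conventions are not all stated.* Sidedness, the way loss enters and the exact form of the adjusted t statistic are left open, so 53% is one point in a range. This stands. No two-sided reading that keeps the clustering reaches 80%, however. A one-sided test reaches it only at 16% and only with a further concession (no +1 term, or no loss). Ignoring clustering also gets there at 16% (82% with full loss and no +1 term), but at 12% only if loss is ignored as well (79.7%). Dropping clustering or loss discards an input that the paragraph says it uses.
- *The paragraph labels 16%, not 12%, as its assumption.* Correct, and the document does not settle which rate was used. Both are reported here.
- *The formula is not the planned analysis.* Section 2 (Data Analysis) specifies individual-level Poisson regression with GEE, and the coefficient of variation is called conservative. With smaller between-group variation power would be higher: at 16%, two-sided, full loss and no +1 term, it is 79% with a coefficient of 0.1. A reader might infer that the trial has close to an even chance of missing a 47% reduction. The documents do not support that. What fails is the planning statement on its own inputs.
- *The fit to 250 per arm.* A reader might infer that the figures were carried over from a trial of about 500 girls. The match is suggestive only. It needs the 12% rate; at 16% the HSV-2 effect fits about 424 girls in total (8.5 × 25 × 2). The Aim 2 range of .55–.7 is not fully reproduced at 250 per arm, and the protocol nowhere mentions a larger size.

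**Conclusion.** The power statement is wrong as written. On the section's own inputs, with six groups per arm and a two-sided 5% test, power at a rate ratio of 0.53 is about 53% at 12% a year or 63% at 16%. The most lenient two-sided handling of the open conventions brings it to 69% or 78%. The effect detectable with 80% power is a ratio of about 0.39 or 0.44.

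These figures grant the full three years. They rest on the Hayes and Bennett rates formula, a coefficient of variation of 0.2 and groups of exactly 25. The two years in the design section lower them to 41% or 50%. Separately, and without any power formula, the 16% rate contradicts both the 22% and the 12% in the same paragraph. Where the printed effects came from is not established, and the finding does not depend on it.

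**What to change.** Keep the sample size, since main-study enrolment is complete. Then, in section 1.a:

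1. Choose one background rate, 16% or 12%, and make the two-year figure and the before-and-after rates agree with it.
2. Reconcile the follow-up: three years in the calculation, two in the General Study Design.
3. State whether the test is one- or two-sided and how the 20% loss enters person-time.
4. Recompute with six groups per arm, and replace both the 80%/0.53 statement and its extension to unintended pregnancy with the result. Call the figure a rate ratio.
5. Add that, on these planning assumptions, a non-significant primary result does not by itself exclude a 47% reduction.

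For orientation (two-sided, +1 term, full 20% loss):

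| Follow-up | Control rate | Power at 0.53 | Ratio detectable at 80% |
|---|---|---|---|
| 3 years | 12% | 53% | 0.39 |
| 3 years | 16% | 63% | 0.44 |
| 2 years | 12% | 41% | about 0.30 |
| 2 years | 16% | 50% | about 0.36 |

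No row should go into the protocol until steps 1 to 3 are settled. The cost is one recalculation, some rewording and a less favourable stated effect; no participants, visits or procedures are added.
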